#### Secondary outcomes

Secondary outcomes include: 1) hip function and 2) HRQL between subjects with and without any type of FAI at 2 years, as determined by the HOS and PedsQL questionnaires [42, 43].

#### Outcome measures

Participants will complete the study questionnaires and undergo a physical examination (at baseline and 6, 12, 18, and 24 months) and MRI (at baseline and 24 months) of their dominant hip. Participants will sync their activity tracker data and send their activity log (at baseline and every 3 months until final follow-up at 2 years) (Table 3).

**Table 3 Tab3:** Schedule of events for the PREVIEW study

Data collection	Enrollment	3 M	6 M	9 M	12 M	15 M	18 M	21 M	24 M
Screening and informed consent	●								
Enrolment data (Demographics)	●								
Physical hip examination	●		●		●		●		●
MRI	●								●
Follow-up form	●		●		●		●		●
Activity tracker wear & synchronization	*	x	x	x	x	x	x	x	x
Activity log	*	x	x	x	x	x	x	x	x
Hip Outcome Score (HOS)	●		●		●		●		●
Pediatric QoL Inventory (PedsQL)	●		●		●		●		●
Adverse events			●		●		●		●

*M* months, *MRI* Magnetic Resonance Imaging, * = 1-week post-enrollment/baseline visit, x = 1-week prior to visit

The physical examination will include range of motion (ROM) measurements in all planes documented in the supine and prone positions by a blinded research assistant (using a goniometer), as well as response of provocative hip tests on both hips [44]. Symptomatic FAI in adolescents is typically characterized by anterior hip pain aggravated by flexion activities, decreased hip internal rotation, and a positive impingement sign [7]. We will define symptomatic FAI using the following criteria: 1) positive impingement with groin pain based on flexion, adduction, and internal rotation (FADIR) test, and 2) decreased ROM: internal rotation of the hip when compared to the contralateral side by 5 degrees [45, 46].

We will use a non-contrast three dimensional (3D)-volumetric interpolated breath-hold examination (VIBE) sequence MRI [47]. This protocol has been used to document FAI-related morphology and eliminates the use of intra-articular contrast injections. All MRI and physical examination information will be provided to an independent radiologist adjudicator to determine the incidence of cam, pincer, or mixed-type FAI according to the pre-specified criteria (Table 2). We will also document the change in cartilage volume, labral pathology, herniation pits on the femoral neck, and the extent of physeal closure as these variables may predict future hip osteoarthritis [44].

The HOS is a self-administered questionnaire designed to capture hip function with clinimetric evidence for use in patients with FAI or labral tears [34, 36, 37]. The HOS was developed for young adults and has been shown to be one of the only hip function questionnaires appropriate for use in adolescents [36, 37, 48]. The PedsQL is a validated and responsive measure of HRQL in children [43]. The PedsQL was specifically designed to measure the core health dimensions outlined by the World Health Organization (physical, emotional, and social functioning), which will ensure generalizability across our global sites [49]. Adult and child versions of the HOS and PedsQL will be completed by a parent and participant at each visit. Adverse events, defined as any symptom, sign, illness, or experience that develops or worsens in severity during the course of this study, will also be documented (Table 3).

### Study follow-up

We will follow participants for 2 years as this timeframe is expected to coincide with the critical period of physeal closure in our study population. In-person follow-up visits will occur at baseline (i.e. time of enrollment), and at 6, 12, 18, and 24 months post-enrollment. Leading up to each follow-up visit, we will ask each participant to wear their activity tracker for 1 week and maintain a daily activity log. At the follow-up visit, we will collect the activity data collected in the week prior, perform a physical hip examination, and ask participants to complete the function and HRQL questionnaires. We will have 4 additional remote activity monitoring visits at 3, 9, 15, and 21 months. Each participant will undergo an MRI of their dominant hip at the baseline and 24-month visits. We designed the follow-up schedule to track activity every 3 months, maintain regular contact with the participants to help minimize loss to follow-up, and at the same time, allow enough time between in-person visits to minimize participant burden.

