### Study outcomes

#### Primary outcome

The primary outcome is the incidence of radiographic FAI between groups at 2 years, as determined by the dedicated MRI of the hip (Table 2). We will identify both symptomatic and asymptomatic cases, where asymptomatic FAI can become symptomatic in young adulthood, and/or could be associated with idiopathic osteoarthritis later in life [41].

**Table 2 Tab2:** Criteria for defining FAI types

FAI type	Criteria
Cam	1. Alpha angle is > 55°; 2. Anterior head-neck offset < 10 mm; 3. Anterior head-neck offset ratio < 0.15 **Must meet 2/3 criteria to be considered cam impingement*
Pincer	1. Acetabular depth < 3 mm; 2. Lateral centre-edge angle > 39°; 3. Acetabular anteversion (in the upper third of the femoral head) < 0° **Must meet 2/3 criteria to be considered pincer impingement*
Mixed	**Must meet 2/3 criteria each for cam and pincer impingement (as per above) to be considered mixed impingement*

*FAI* Femoroacetabular impingement

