### Statistical plan

#### Primary analysis

As previously described, study groups will be defined at the completion of follow-up given participant activity levels may change over time. The proportion of subjects developing FAI in the sport specialist group versus non-sport specialist group will be compared using a logistic regression analysis with FAI as the dependent variable and will include the following independent variables: activity level (sport specialist versus non-sport specialist), body mass index (BMI), and sex. Results will be reported as odds ratios (OR) with 95% confidence intervals and associated *p*-values.

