#### Secondary analyses

We will perform independent samples t-tests to test for differences in 24-month HOS and PedsQL scores between participants who do and do not develop FAI within the 24-month follow-up period. These analyses will be repeated comparing participants who do and do not develop symptomatic FAI. Each secondary outcome will be quantified using descriptive statistics and 95% confidence intervals. We will use multiple imputation to handle missing data.

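### FAI is read on the dominant hip only but serves as the child's FAI status in the HOS and PedsQL comparisons, so the no-FAI group can hold undetected FAI of the other hip

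*Protocol article*

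**What the plan says.** **Imaging.** Study follow-up states: "Each participant will undergo an MRI of their dominant hip at the baseline and 24-month visits". Outcome measures agrees: "MRI (at baseline and 24 months) of their dominant hip".

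**Definition of FAI.** Under Primary outcome: "The primary outcome is the incidence of radiographic FAI between groups at 2 years, as determined by the dedicated MRI of the hip". Every criterion in Table 2, for cam, pincer and mixed type, is a morphological measurement. The adjudicator also receives the physical examination, but no Table 2 criterion uses it.

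**Unit of analysis.** The Primary analysis compares "The proportion of subjects developing FAI in the sport specialist group versus non-sport specialist group". Secondary outcomes sets out hip function and "HRQL between subjects with and without any type of FAI at 2 years". Secondary analyses uses t-tests on "24-month HOS and PedsQL scores between participants who do and do not develop FAI within the 24-month follow-up period" and repeats them for symptomatic FAI.

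**Side of the other measures.** The article presents the PedsQL as a measure of the child's quality of life and names no side for the HOS. The physical examination covers range of motion "as well as response of provocative hip tests on both hips". Symptomatic FAI needs a positive FADIR test with groin pain and internal rotation 5 degrees below the opposite hip. The article does not say that the affected side must be the scanned one, or how a positive finding in the unscanned hip is handled.

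**The concern.** One hip determines FAI status, while the score compared with it belongs to the whole child or to a hip that is not named. A child with FAI only in the non-dominant hip therefore enters the secondary t-tests in the reference group. If that hip lowers function or quality of life, the reference mean falls and the FAI versus no-FAI difference shrinks. The error pushes toward concluding that FAI does not affect function or quality of life, which is the question of the secondary objectives. The Discussion also says that the sample size secures power for hip function and HRQL, so a diluted null result could be read as informative.

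For the primary outcome the issue is only the label. A proportion measured on one hip would be reported as though it described the child.

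**Working it through.** **1. The plan's own figure.** Sample size calculation gives 40% and 15%, two-sided alpha 0.01, 80% power and 81 per group. The mean risk is 0.275 and the difference 0.25.

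- Uncorrected: n = [2.576 × √(2 × 0.275 × 0.725) + 0.842 × √(0.40 × 0.60 + 0.15 × 0.85)]² / 0.25² = 73.05, rounded up to 74.
- With continuity correction: (73.05/4) × [1 + √(1 + 4/(73.05 × 0.25))]² = 80.9, rounded up to 81.

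The 81 reproduces, so the sample size arithmetic is not at fault.

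**2. Share of the no-FAI group with FAI in the other hip.**

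From the article: dominant-hip risk p = 0.40 for specialists and 0.15 for non-specialists.

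Assumed, because the article gives no bilateral rate:
- the same risk p in each hip;
- exposure groups of equal size;
- within-group between-hip correlation ρ from 0.3 to 0.7.

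Formulas:
- P(both hips) = p² + ρp(1 − p)
- P(other hip has FAI, given scanned hip negative) = (p − P(both)) / (1 − p) = p(1 − ρ)

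The no-FAI group mixes both exposure groups in proportion to their scan-negative children, 0.60 and 0.85, which sum to 1.45.

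| ρ | Specialists | Non-specialists | No-FAI group overall |
|---|---|---|---|
| 0.3 | 28% | 10.5% | (0.60 × 0.28 + 0.85 × 0.105)/1.45 = 17.7% |
| 0.5 | 20% | 7.5% | (0.60 × 0.20 + 0.85 × 0.075)/1.45 = 12.7% |
| 0.7 | 12% | 4.5% | (0.60 × 0.12 + 0.85 × 0.045)/1.45 = 7.6% |

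With 81 per group, the no-FAI group has 81 × 1.45 ≈ 117 children. Of these, about 21 (ρ = 0.3) down to 9 (ρ = 0.7) would have FAI in the unscanned hip.

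**3. A second way to set the assumption.** Let b be the chance that the other hip has FAI when one hip has it, the same in both exposure groups. The share is then 0.275(1 − b)/0.725, which is 19% at b = 0.5, 4% at b = 0.9 and zero at b = 1.

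**4. Effect on the score difference.** Let Δ be the true mean difference, c the share from step 2, and suppose FAI in either hip or both lowers the score equally. The observed difference is (1 − c)Δ, about 82% to 92% of Δ.

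The article gives no target difference for HOS or PedsQL. As an illustration, take a difference that would have 80% power at two-sided alpha 0.01, so that its standardised size is 2.576 + 0.842 = 3.418:

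- c = 0.177: 3.418 × 0.823 − 2.576 = 0.24, power about 59%.
- c = 0.076: 3.418 × 0.924 − 2.576 = 0.58, power about 72%.

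If FAI in the unscanned hip is silent, it does not lower the score and the loss is smaller.

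**The case against.** The strongest reply is that this is a disclosed index-joint design. The article says twice that the MRI is of the dominant hip, and the primary outcome refers to one hip. Study committees and monitoring has the outcome adjudicated blind to activity level. For the primary analysis this stands: a fixed hip, read the same way in every child, supports a valid comparison of exposure groups.

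A reader might go further in three ways that the documents do not support.

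- **That 40% and 15% are wrong as risks.** Under the assumptions above, either-hip risk, 2p − P(both), would be 57% to 47% and 24% to 19%. But the article never presents 40% and 15% as either-hip risks. It calls them the pilot's event rate for the primary outcome, and the natural reading is that they were measured in the same way.
- **That a painful unscanned hip is misclassified FAI.** Pain without FAI morphology belongs in the no-FAI group under Table 2. Only undetected morphology is misclassified.
- **That more undetected FAI among specialists itself biases the secondary tests.** Those tests compare FAI with no FAI, not specialists with non-specialists. What matters is the overall share.

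Two further replies stand in part. The full protocol or case report form may fix the side of the HOS, so that half is less certain; the PedsQL cannot be tied to a side. The definition of symptomatic FAI does imply an index hip and a comparator, but it does not say that the index hip is the scanned one. Finally, the size is assumed throughout. Enrolled children are asymptomatic and the outcome counts asymptomatic FAI, so the equal-effect assumption gives an upper limit.

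**Conclusion.** The point holds for the secondary analyses and, as a matter of naming, for the primary outcome. The HOS and PedsQL comparisons use a reference group that can contain FAI of the unscanned hip, and this biases the differences toward zero. With equal risk in both hips, equal exposure groups and a within-group correlation of 0.3 to 0.7, the share is about 18% down to 8%. The alternative assumption in step 3 extends the lower end to 4%. The differences shrink by up to that fraction if either hip lowers scores equally, and by less if the unscanned hip's FAI is asymptomatic. The effect vanishes only if FAI is always bilateral or the unscanned hip never affects the score.

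The primary between-group comparison is not invalidated, and nothing here shows the sample size to be wrong. This is an inexpensive improvement to the plan, not a flaw in its main test.

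**What to change.** 1. State the primary outcome and the conclusions drawn from it as FAI of the dominant hip.
2. Instruct participants and parents to answer the HOS for the scanned hip, if the form does not already do so.
3. For the analysis, count symptomatic FAI only when the positive FADIR test and the reduced internal rotation are on the scanned side.
4. Add a sensitivity analysis of 24-month HOS and PedsQL that excludes children with a positive provocative test in the unscanned hip from both the FAI and the no-FAI groups. Excluding them from the no-FAI group alone would remove low scorers from one side only and inflate the difference.

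The sensitivity analysis cannot remove silent FAI of the unscanned hip, so it should be reported beside the main result, with the one-hip limitation stated.

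Cost: some wording, one instruction on the HOS form and one extra analysis of examinations already planned on both hips. The headline claim narrows to one hip, and the sensitivity analysis has slightly fewer children. No further imaging is needed.

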### Sample size calculation

We have based our sample size calculation on our pilot study data (*N* = 53), where the primary outcome event rate (incidence of FAI) is 40% for the sport specialists at the MVPA level (group 1) and 15% for the non-sport specialists at all physical activity levels (group 2). These proportions very closely match prior cross-sectional research that evaluated the incidence of FAI among athletes [10]. Because we have looked at early data from the pilot study to inform our calculation, we have adjusted our type I error rate. To achieve 80% power for a two-sided test at alpha = 0.01, we will require a sample size of 81 in each exposure group (Table 4). Given that some participants’ activity levels may change during the course of the study (where they may change from sport specialist to non-specialist, or vice versa), we will increase the sample size by 10% to ensure we have at least 81 participants in each exposure group. We will also account for a 5% rate of ineligibility (due to a mature hip [closed physes] found on the baseline MRI) and a 10% loss to follow-up rate. Therefore, we require a total sample size of 200 participants. The pilot participants will be rolled into the definitive study.

**Table 4 Tab4:** Per group sample sizes. 80% power, alpha = 0.01, 2-sided testing

	FAI risk in non-sports specialists		
	5%	15%	25%

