#### Subgroup/sensitivity analyses

To assess whether the magnitude of the effect of sport activity on the development of FAI is significantly different in males than in females, we will add an interaction term between sex and sport specialist versus non-sport specialist to the primary logistic regression model. We hypothesize that sport specialization will be more strongly associated with incidence of FAI in males than in females.

No interim analyses are planned. All tests will be 2-sided with α = 0.01. We will use SAS 9.4 (Cary, NC) to perform all analyses.

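### The pilot participants whose group rates set the effect size also enter the primary model; alpha = 0.01 limits false positives but leaves the pooled odds ratio and its 95% CI pulled toward the pilot result

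*Protocol article*

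**What the plan says.** All of this comes from the protocol article.

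- **Sample size calculation.** The assumed FAI rates, 40% in sport specialists and 15% in non-specialists, are those seen in a pilot of 53. On the consequence of that look: "Because we have looked at early data from the pilot study to inform our calculation, we have adjusted our type I error rate". On the size: "To achieve 80% power for a two-sided test at alpha = 0.01, we will require a sample size of 81 in each exposure group". On the pilot cohort: "The pilot participants will be rolled into the definitive study".
- **Primary analysis.** FAI is modelled by logistic regression on exposure group, BMI and sex. The result is an odds ratio with a 95% CI and a p-value. Pilot participants are not treated separately.
- **Subgroup/sensitivity analyses.** "No interim analyses are planned", and "All tests will be 2-sided with α = 0.01".

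The article gives no derivation of 0.01 and does not state the level from which it was lowered. It does not say how many of the 53 had 24-month outcomes when the rates were read.

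**The concern.** The data that suggested a 25-point difference are used again to estimate and test that difference. A lower significance level changes how often the null hypothesis is rejected. It does not change the point estimate, and here the interval stays at 95%. The pooled odds ratio therefore mixes new evidence with the result that prompted the design. If the true association is weaker than in the pilot, the estimate is expected to be too large. The odds ratio is what readers will take away about sport specialization and FAI, and nothing in the stated analysis shows how much of it comes from the pilot.

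**Working it through.** **Inputs from the protocol.** Pilot N = 53; rates 0.40 and 0.15; two-sided alpha 0.01; 80% power; 81 per group; total 200; 5% ineligibility; 10% loss to follow-up.

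**Assumptions.** Pilot counts of 8/20 and 5/33 (they give 40% and 15%); complete pilot outcomes; an unadjusted alpha of 0.05; equal groups and an unadjusted comparison of proportions for power.

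**1. The plan's own figure.** With d = 0.25 and mean rate 0.275,

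n = [2.576·√(2·0.275·0.725) + 0.842·√(0.40·0.60 + 0.15·0.85)]² / 0.25² = 73.05.

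The continuity correction, (n/4)·[1 + √(1 + 4/(n·d))]², gives 80.85, so 81 per group. The stated figure is reproduced, and power below uses the same convention.

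**2. Share of pilot participants.** Applying both allowances to everyone gives 200 × 0.95 × 0.90 = 171 analysed. Of these, 53 × 0.95 × 0.90 ≈ 45 are from the pilot and 147 × 0.95 × 0.90 ≈ 126 are new. The pilot share is 45/171 = 0.263. If instead all 53 are among the required 162, it is 53/162 = 0.327, with 109 new.

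**3. Pull on the estimate.** If pilot and new participants have the same exposure mix, the expected pooled risk difference exceeds the truth by share × (0.25 − true difference).

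- True difference 15 points: 0.263 × 10 = 2.6 points.
- True difference zero: 0.263 × 25 = 6.6 points.
- At the larger share of 0.327: 3.3 and 8.2 points.

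This is on the risk-difference scale. The odds ratio is pulled in the same direction.

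**4. False positives given the pilot.** Pilot z = (0.400 − 0.152) / √[(13/53)(40/53)(1/20 + 1/33)] = 2.04. With t the pilot share and no true effect among new participants,

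P(reject) = P(Z > (2.576 − √t × 2.04)/√(1 − t)).

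- t = 0.263: P(Z > 1.78) = 0.037.
- t = 0.327: P(Z > 1.72) = 0.043.

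At 0.05 with t = 0.327, the same calculation gives 0.167.

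**5. Power: pooled at 0.01 against new participants only at 0.05.** For n per group, set m = n − 2/d + 1/(n·d²) and enter m in the uncorrected power formula.

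| True rates | Analysed: pooled / new | Pooled, 0.01 | New only, 0.05 |
|---|---|---|---|
| 40% v 15% | 171 / 126 | 82.9% | 84.7% |
| 40% v 15% | 162 / 109 | 80.1% | 78.2% |
| 35% v 15% | 162 / 109 | 57.4% | 59.3% |
| 30% v 15% | 162 / 109 | 31.4% | 37.5% |
| 50% v 15% | 162 / 109 | 98.5% | 96.9% |

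At the design effect the difference is about 2 points either way, and its sign depends on how many pilot participants are analysed. New-only is ahead at the smaller effects shown, and pooled is ahead at the larger one.

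**The case against.** The protocol discloses the look and pays for it in alpha, which is a recognised trade. The payment is adequate for the test: even conditional on a favourable pilot, the false-positive rate of about 4% stays under 5%. A reader might infer that the type I error is uncontrolled, and the arithmetic does not support that. The 4% is higher than the nominal 1%, but only because it conditions on a pilot that already came out favourably.

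A reader might also see a contradiction between the pilot look and the statement that "No interim analyses are planned". There is none. That sentence concerns future looks, and the past one is stated openly under the sample size calculation. Renaming it would change nothing.

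The pilot figures used here are partly assumed. The Discussion reports only that pilot enrolment was completed, and exposure groups are fixed at the end of follow-up. How many of the 53 had final outcomes and classification is therefore unknown. This stands, and it makes the sizes above illustrative. The direction of the pull does not depend on it, provided the true difference is below 25 points.

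Finally, the missing derivation of 0.01 may be in the full protocol, and a sensitivity analysis without the pilot may be in an analysis plan not shown here. If that analysis is already pre-specified, nothing remains to be done.

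None of these objections removes the pull on the pooled odds ratio or on its 95% CI.

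**Conclusion.** The point holds for the estimate, not for the test. Reusing the pilot participants is expected to shift the pooled risk difference upward by about 2.6 points if the truth is 15 points, and by about 6.6 if it is zero, with 45 of 171 analysed from the pilot. Alpha = 0.01 does not correct this.

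Two stronger readings are tempting. The first is that the alpha penalty costs more power than the pilot data add. That is not established: at 40% v 15% the two roughly cancel, and pooling is slightly ahead when all 53 are among 162 analysed. The comparison also rests on an unadjusted alpha of 0.05, which the protocol does not state.

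The second is that the pilot must be removed from the primary analysis. That is a trade-off and not a correction. Compared at the same 95% level, the interval on 171 is about 14% narrower than on 126 (√(126/171) = 0.858). Setting a 95% interval on 126 against a 99% interval on 171 would hide this, and the protocol reports 95% intervals.

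What remains is a cheap improvement worth making. It is not a defect that invalidates the primary test.

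**What to change.** Keep the pooled primary test at two-sided 0.01. Before 24-month outcomes are analysed, pre-specify the same logistic model (exposure group, BMI, sex) fitted without the 53 pilot participants. Report its odds ratio and CI beside the pooled result. State in advance that the claim of association will be qualified if the two odds ratios lie on opposite sides of 1.

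The cost is a sentence or two in the plan and one extra model, with no added participants. The non-pilot estimate uses about 45 to 53 fewer participants, so it is less precise: its standard error is about 16% larger at 126 than at 171 (√(171/126) = 1.165), and about 22% larger at 109 than at 162 (√(162/109) = 1.219). It should therefore be read for direction and size, not as a second significance test.

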#### Defining sport specialization

Sport specialization will be defined according to the American Orthopaedic Society for Sports Medicine (AOSSM) and American Medical Society for Sports Medicine (AMSSM) early sport specialization criteria (Table 1) [28, 33]. At the baseline/enrollment visit, we will collect information about any current sport participation, including type(s) and frequency, for each participant. One week prior to each follow-up visit, we will ask participants and their parent(s) to complete a daily activity log to record all types of sport activity the participant engaged in (e.g. games, practices, both organized and unorganized), or lack thereof.

**Table 1 Tab1:** Definition of study groups according to objective measurement and guideline criteria

Study group	AOSSM criteria [28]	Activity tracker criteria	Duration
Group 1: Sport specialist, MVPA	1. Participation in intensive training and/or competition in organized sports greater than 8 months per year (essentially year round) [29] 2. Participation in **1 sport** to the exclusion of participation in other sports (limited free play overall) [30] 3. Involving prepubertal (seventh grade or roughly age 12 years) children.	Greater than 180 accumulated minutes of MVPA [31, 32] during participation in one sport type across one week of activity tracking	Meets criteria within either one or both years of follow-up
Group 2: Non-sport specialist, any activity level	1. Participation in **more than 1 sport** at any physical activity level **OR** 2. Participation in **none or low** training and/or competition in organized sports for any period of time. 3. Involving prepubertal children.	Greater than or less than 180 accumulated minutes of MVPA across one week of activity tracking	Meets criteria during both years of follow-up

*AOSSM* American Orthopaedic Society for Sports Medicine, *MVPA* moderate-to-vigorous physical activity

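### The total of 200 is rounded below every combination of the stated allowances, and under the Table 1 duration rule inflating the total cannot secure 81 participants in each exposure group

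*Protocol article*

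**What the plan says.** The Sample size calculation section takes its FAI rates from the pilot study. The rate "is 40% for the sport specialists at the MVPA level (group 1") and "15% for the non-sport specialists at all physical activity levels (group 2"). The design target is set as "To achieve 80% power for a two-sided test at alpha = 0.01", which gives 81 per group, or 162 in all.

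Three allowances follow:

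- **Change of group.** Participants may move between specialist and non-specialist in either direction, so "we will increase the sample size by 10% to ensure we have at least 81 participants in each exposure group".
- **Ineligibility.** "We will also account for a 5% rate of ineligibility (due to a mature hip [closed physes] found on the baseline MRI").
- **Loss to follow-up.** 10%.

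The section then concludes "Therefore, we require a total sample size of 200 participants" without showing how the allowances were combined.

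Table 1 (Defining sport specialization) fixes how long the criteria must be met. For group 1 the rule is "Meets criteria within either one or both years of follow-up"; for group 2 it is "Meets criteria during both years of follow-up". The Defining activity level and Primary analysis sections add that groups are assigned only when follow-up is complete.

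**The concern.** There are two linked problems.

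First, a number meant to guarantee a minimum should be rounded up, and 200 appears to be rounded down. The margin kept for group changes is then smaller than the one the text describes.

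Second, the 10% increase treats group change as symmetric, while the classification rule is not. A participant who is a specialist in one follow-up year and not in the other goes to group 1, whichever year came first. A larger total does not protect the smaller group against such a rule.

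At stake is whether the planned group sizes, and the power attached to them, are what 200 enrolled participants will deliver.

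**Working it through.** **Inputs (Sample size calculation):** p1 = 0.40, p2 = 0.15, two-sided alpha = 0.01 (z = 2.576), power 80% (z = 0.842), allowances 10%, 5% and 10%, stated total 200.

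**Step 1. Reproduce 81.** With mean rate 0.275,

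n = [2.576·√(2·0.275·0.725) + 0.842·√(0.40·0.60 + 0.15·0.85)]² / 0.25² = 73.05.

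With the continuity correction,

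n_c = (n/4)·[1 + √(1 + 4/(n·0.25))]² = 80.85, rounded up to 81.

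The same corrected formula reproduces every cell of Table 4, so the per-group figure is sound.

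**Step 2. Build the total from 2 × 81 = 162.**

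| Way of combining the allowances | Calculation | Total |
|---|---|---|
| Added | 162 × 1.25 | 202.5 |
| Compounded | 162 × 1.10 × 1.05 × 1.10 | 205.8 |
| +10%, then division for the two losses | 162 × 1.10 / (0.95 × 0.90) | 208.4 |
| Division throughout | 162 / (0.90 × 0.95 × 0.90) | 210.5 |

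Rounded up, these are 203, 206, 209 and 211. All exceed 200.

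**Step 3. Work forward from 200.** 200 × 0.95 × 0.90 = 171 evaluable, or 85.5 per group if split evenly. The margin over 162 is 171/162 − 1 = 5.6%. A full 10% margin would be 162 × 1.10 = 178.

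**Step 4. Apply the Table 1 rule.** A participant meeting the specialist criteria in one follow-up year only counts in group 1. From an assumed even start of 85.5, group 2 can lose 85.5 − 81 = 4.5 participants (5.3% of the group) before reaching 81, so a net move of five takes it below. An assumed net move of 10% gives 85.5 × 1.10 = 94 and 85.5 × 0.90 = 77. An assumed 20% gives 103 and 68.

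**Step 5. Power at these splits of 171.** For group sizes n1 and n2 and pooled rate p̄ = (n1·p1 + n2·p2)/(n1 + n2),

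power = Φ{[0.25 − c − 2.576·√(p̄(1 − p̄)(1/n1 + 1/n2))] / √(p1(1 − p1)/n1 + p2(1 − p2)/n2)},

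with c = ½(1/n1 + 1/n2) for the corrected version and c = 0 for the uncorrected one. As a check, 81/81 gives 80% corrected.

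| Specialists / non-specialists | Corrected | Uncorrected |
|---|---|---|
| 85.5 / 85.5 | 83% | 87% |
| 94 / 77 | 82% | 86% |
| 103 / 68 | 79% | 84% |
| 114 / 57 | 74% | 80% |
| 57 / 114 | 79% | 84% |

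At a 2:1 split the direction matters. An excess of specialists, which is where the Table 1 rule pushes, costs more than an excess of non-specialists.

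**The case against.** The best defence is that 200 is a rounded sum. Simple addition gives 202.5, only 1.2% above it, and compounding gives 205.8, 2.9% above. The text does not say which method was used, so it would be too strong to say that 200 bears no relation to the allowances. That stands. What remains is that the rounding goes down, in a calculation meant to secure a minimum.

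A reader might go further and count the 10% for group change as a third loss: 200 × 0.95 × 0.90 × 0.90 = 154, or 77 per group, with 77% corrected power. The documents do not support this. Participants who change activity are reclassified at the end of follow-up, have their MRI and enter the logistic model. The evaluable number is 171, which at an even split meets both the 81 and the 80% target.

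A reader might also infer that every change of status ends in group 1. That is too strong as well. Table 1 refers to years of follow-up, not to status at enrolment. Someone enrolled as a specialist who meets the criteria in neither follow-up year falls in group 2. The rule favours group 1, but group 2 can gain members.

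Finally, recruitment targets by sport status may well stand in the full protocol, so their absence from a condensed article is no fault. The point here is narrower: the article itself promises a per-group minimum and gives an inflation of the total as the means of achieving it.

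**Conclusion.** The concern holds as a modest arithmetic shortfall plus a group-size guarantee that the stated design does not deliver. The total is 3 to 11 participants below what the allowances imply, depending on how they are combined, and the margin left for reclassification is 5.6% instead of 10%. Under Table 1, reclassification mainly drains group 2, and a small net move is enough to take it below 81.

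This is not a serious loss of power. Corrected power stays at about 80% or above up to a split near 103/68, and falls clearly below it only when specialists strongly predominate.

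The Step 2 and Step 3 figures rest only on the protocol's numbers. The even start, the 10% and 20% net moves and the 2:1 splits are assumptions, because the document gives neither an expected nor a pilot split. The power figures are for an unadjusted comparison of two proportions, as in the protocol's own calculation.

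**What to change.** In the Sample size calculation section:

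1. State how the allowances are combined. Then either keep 200 and say that it yields about 171 evaluable participants, or give the total that the chosen method implies (203 to 211).
2. Replace the guarantee of 81 in each exposure group with the final split expected under the Table 1 duration rule, the assumption behind it, and the power at that split.
3. Monitor the running split by activity status during recruitment, so that a marked excess of specialists is seen while it can still be corrected.

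If 200 is kept, the cost is a few sentences and a running tabulation, with no added participants. If the total is corrected instead, it is 3 to 11 more participants.
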